## SAP Revision History

| Protocol version | Updated SAP version no. | Section number changed | Description and reason for change | Date changed |
|------------------|-------------------------|------------------------|-----------------------------------|--------------|
|                  |                         |                        |                                   |              |
|                  |                         |                        |                                   |              |
|                  |                         |                        |                                   |              |
|                  |                         |                        |                                   |              |

## 1. BACKGROUND

### 1.1 RATIONALE AND RESEARCH QUESTION

See protocol.

### 1.2 OBJECTIVES

To determine whether, at an NHS Trust level, having a suspected COVID-19 assessment pathway which incorporated PCT testing, modified the impact of the first COVID-19 wave on antibiotic use (both on a predefined set of antibiotics used for community-acquired pneumonia (CAP) and total antibiotics).

## 2. STUDY MATERIALS

### 2.1 STUDY DESIGN

Controlled, multi-centre, retrospective observational, aggregated (Trust level) data, interrupted time series analysis to assess the change in level and/or trend of antibiotic use, adjusted for hospital activity (e.g. admissions and bed days), following the introduction of PCT testing.

## 2.2 RANDOMISATION

Not applicable.

## 2.3 SAMPLE SIZE

Specifying a formal sample size target is not possible as this is an opportunistic retrospective analysis of antibiotic prescription data provided by our partners Rx Info Ltd, Public Health England (PHE) and Public Health Wales (PHW). Data will be available for around 100-120 English NHS Trusts and around 15-20 Welsh NHS hospitals, with up to 19 weekly data points for each.

## 2.4 FRAMEWORK

Retrospective analysis of routinely collected data.

## 2.5 INTERIM ANALYSES

### 2.5.1 PLANNED SAMPLE SIZE ADJUSTMENT

Not applicable.

### 2.5.2 STOPPING RULES

Not applicable.

## 2.6 TIMING OF FINAL ANALYSIS

Once all data have been made available by our partners.

## 2.7 TIMING OF OUTCOME ASSESSMENT

We will use aggregated data from acute admissions to Trusts between ISO weeks 9-27 (24 February 2020 to 05 July 2020 inclusive) to encompass the first peak of the COVID-19 pandemic across the UK.

# 3. STATISTICAL PRINCIPLES

## 3.1 LEVELS OF CONFIDENCE AND P-VALUES

All hypothesis tests and confidence intervals (CIs) will be two-sided. We will use a 5% significance level and present 95% CIs.

### 3.1.1 ADJUSTMENT FOR MULTIPLICITY

Not applicable.

## 3.2 ADHERENCE AND PROTOCOL DEVIATIONS

### 3.2.1 DEFINITION AND ASSESSMENT OF ADHERENCE

Not applicable.

#### 3.2.2 PRESENTATION OF ADHERENCE

Not applicable.

#### 3.2.3 DEFINITION OF PROTOCOL DEVIATION

Not applicable.

#### 3.2.4 PRESENTATION OF PROTOCOL DEVIATIONS

Not applicable.

### 3.3 ANALYSIS POPULATION

To reduce the risk of bias, we will use data from all acute and teaching NHS hospital Trusts (i.e. excluding specialist hospitals) in England and Wales caring for COVID-19 inpatients over 16 years of age between 24 February 2020 and 05 July 2020. Routine hospital activity has markedly reduced during COVID-19 (e.g. cancellation of elective work) and this will have affected antibiotic prescribing and makes the pre-COVID-19 prescribing data invalid for comparison. In addition, PCT testing is expected to impact primarily on suspected COVID-19 patients who will only make up a proportion of inpatients at any one time. Hospital activity data will therefore be used to control for reduced inpatient activity.

## 4. STUDY POPULATION

### 4.1 SCREENING DATA

Not applicable.

### 4.2 ELIGIBILITY

Not applicable.

### 4.3 RECRUITMENT

Not applicable.

### 4.4 WITHDRAWAL/FOLLOW UP

#### 4.4.1 LEVEL OF WITHDRAWAL

Trusts with incomplete essential information (see 4.4.3) will be fully excluded from the analysis.

#### 4.4.2 TIMING OF WITHDRAWAL

These Trusts will be removed prior to the analysis.

#### 4.4.3 REASONS FOR WITHDRAWAL

A Trust will be excluded if essential information about the intervention, such as the level of use of PCT testing during the first wave of COVID-19 or the date of introduction of PCT testing, cannot be obtained.

#### 4.4.4 PRESENTATION OF WITHDRAWAL/LOSS TO FOLLOW-UP

Numbers of Trusts excluded from the analysis and reasons for exclusion will be listed in a table and/or presented in a CONSORT flow diagram.

### 4.5 BASELINE PARTICIPANT CHARACTERISTICS

#### 4.5.1 LIST OF BASELINE DATA

‘Baseline’ data include:

- number of Trusts included in the analysis
- hospital admissions (total and COVID-positive) between ISO weeks 9 and 27 per Trust
- hospital bed days (total and COVID-positive) between ISO weeks 9 and 27 per Trust
- antibiotic use (tDDD and CAP-DDDs, see 5.1) between ISO weeks 9 and 27 per Trust

#### 4.5.2 DESCRIPTIVE STATISTICS

Descriptive (e.g. means or medians with standard deviations or interquartile ranges for continuous variables, frequencies and percentages for binary or categorical variables) and graphical summaries (e.g. boxplots) will be presented by country (England or Wales) and by exposure to PCT testing: 1) Trusts not using PCT (routinely) between ISO weeks 9 and 27 (‘never-users’), 2) Trusts using PCT in either or both of ICU and ED/acute wards at the beginning of the first wave (ISO week 9) and continuing to do so until ISO week 27 without increasing the level of usage (‘always-users’), 3) Trusts introducing PCT use for the first time or increasing PCT use (e.g. from use in ICU only to use in ICU and ED/acute wards) between ISO weeks 9 and 27 (‘adopters’).

## 5. ANALYSIS

### 5.1 OUTCOME DEFINITIONS

#### 5.1.1 PRIMARY OUTCOME(S)

Weekly trend of:

- number of defined daily doses (DDDs) of all antibiotics excluding anti-TB drugs, etc. (total DDDs, ‘tDDD’) per total number of admissions

#### 5.1.2 TIMING, UNITS AND DERIVATION OF PRIMARY

Aggregated weekly antibiotic usage data (total dispensing to hospital locations) will be collected from Rx Info Ltd (and provided via PHE and PHW), and weekly patient activity data will come directly from PHE and PHW. As a consequence of the extraction and aggregation methods differing between PHE and PHW (as described in separate documents), English and Welsh data will be analysed separately.

Date of introduction of PCT testing, or not, and whether a Trust that did not introduce PCT testing between March and June 2020 was using it already or not, will be collected via direct contact with hospitals in WP 1.1. For the Trusts introducing PCT testing, their first week of PCT use will be defined as the ISO week following the reported introduction date.

The three different data elements (antibiotic usage, patient activity, PCT usage) will be merged to create a single analysis dataset; this will be done by matching their NHS Organisational Data Service (ODS) codes.

tDDDs are defined as all ATC J01, J04AB02 (rifampicin), A07AA12 (fidaxomicin) and A07AA09 (vancomycin – oral).

### 5.1.3 LIST OF SECONDARY OUTCOMES

Weekly trend of:

- number of prespecified antibiotics commonly used for respiratory tract infection (community-acquired pneumonia, ‘CAP-DDDs’) per total number of admissions
- number of tDDDs per total number of patient bed days
- number of CAP-DDDs per total number of patient bed days
- number of tDDDs per number of COVID-positive admissions
- number of CAP-DDDs per number of COVID-positive admissions
- number of tDDDs per number of COVID-positive patient bed days
- number of CAP-DDDs per number of COVID-positive patient bed days

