### 5.2.6 SUBGROUP ANALYSES

The outcomes defined in section 5.1 will be further subclassified, allowing us to analyse weekly trend of:

- number of DDDs of antibiotics by classification (broad spectrum, narrow spectrum)
- number of DDDs of antibiotics by route (IV, oral)
- number of DDDs of antibiotics by WHO 'AWaRe' category (Access, Watch, Reserve)
- number of DDDs of antibiotics by individual agent (in the list of CAPs, see 5.1.2)

per

- number of COVID-positive admissions
- total number of admissions
- number of COVID-positive patient bed days
- total number of patient bed days

Additionally, COVID-positive admissions and patient bed days will be further split into:

- admitted COVID-positive (<14 days pre-admission) or COVID-positive ≤day 7 post-admission)
- COVID-positive >day 7 post-admission

Furthermore, we will perform a separate analysis including critical care patients only.

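### Four of the seven secondary outcomes divide all-patient antibiotic use by COVID-positive activity, so their time course is dominated by the epidemic curve and they are undefined at zero

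*SAP*

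**What the plan says.** SAP 5.1.3 crosses two numerators (tDDDs and CAP-DDDs) with total and COVID-positive admissions and bed days. One of the eight combinations is the primary outcome and seven are secondary. Four of the seven have a COVID-positive denominator: tDDDs and CAP-DDDs over admissions ("number of CAP-DDDs per number of COVID-positive admissions") and over bed days ("number of CAP-DDDs per number of COVID-positive patient bed days").

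SAP 5.1.5 refers back to 5.1.2 for derivation, where the numerator is described as "Aggregated weekly antibiotic usage data (total dispensing to hospital locations) will be collected from Rx Info Ltd". No numerator restricted to COVID-19 patients is defined. SAP 3.3 acknowledges that PCT testing is aimed at "suspected COVID-19 patients who will only make up a proportion of inpatients at any one time".

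The unit is the Trust-week, "with up to 19 weekly data points for each" (SAP 2.3). The window was chosen "to encompass the first peak of the COVID-19 pandemic across the UK" (SAP 2.7).

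SAP 5.2.1 fits a linear mixed model in ISO week, with PCT use by setting and its interaction with week, and tests for a change in level and in slope. SAP 5.2.2 plans no covariate adjustment. SAP 5.2.4 allows extra week terms, such as a quadratic, if the trend is clearly non-linear. SAP 5.3 only describes missingness. SAP 5.2.6 reuses the COVID-positive denominators by spectrum, route, AWaRe category and agent, and states that "COVID-positive admissions and patient bed days will be further split into" two groups at day 7.

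**The concern.** Numerator and denominator describe different patients. If prescribing per admission is constant while the COVID-positive share rises and falls, the ratio falls and rises as the reciprocal of that share. Some Trusts introduced PCT while the share was moving, so the model can attribute part of this movement to PCT. The stated purpose of the activity data in SAP 3.3 is to control for reduced inpatient activity, and COVID-positive counts do not measure that.

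A Trust-week with no COVID-positive patients has no value at all. With no rule in the SAP, those weeks would be dropped or patched at the analyst's discretion. The day-7 split in 5.2.6 makes the denominators smaller still.

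At stake is whether the level and trend tests on these four outcomes, and on their many 5.2.6 versions, say anything about PCT.

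**Working it through.** **1. Window (the SAP's own figure).** 24 February 2020 is the Monday of ISO week 9 and 5 July 2020 is the Sunday of ISO week 27. 27 - 9 + 1 = 19 weeks, which matches SAP 2.3.

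**2. Count.** COVID-positive admissions: 2 outcomes. COVID-positive bed days: 2 outcomes. Total 4 of 7.

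**3. Identity.** Let D be DDDs, A total admissions, C COVID-positive admissions and p = C/A. Then D/C = (D/A)/p. The same holds for bed days, with p the COVID-positive share of bed days. Assume a constant 3 DDDs per admission:

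| COVID-positive share | D/C |
|---|---|
| 1% | 3/0.01 = 300 |
| 10% | 3/0.10 = 30 |
| 30% | 3/0.30 = 10 |

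That is a 30-fold range with no change in prescribing.

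**4. Range over a wave (assumed).** DDDs are held constant and weekly COVID-positive admissions follow a bell curve peaking in week 15 with SD 3 weeks. The largest ratio divided by the smallest over weeks 9 to 27 is:

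| Floor to peak of weekly admissions | Max/min of ratio |
|---|---|
| 3 to 40 | 13.3 |
| 1 to 40 | 39.5 |
| 1 to 100 | 96.8 |

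On the log scale, the denominator's share of the variance over time is Var(log C) / [Var(log C) + log(1 + CV²)]. With floor 1, peak 10 to 100 and a DDD coefficient of variation of 5% to 20%, this is 94.7% to 99.9%.

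**5. Zero denominators (assumed Poisson counts).** P(C = 0) = exp(-m) for a weekly mean of m admissions:

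| m | P(zero) |
|---|---|
| 0.5 | 0.61 |
| 1 | 0.37 |
| 2 | 0.14 |
| 3 | 0.05 |
| 5 | 0.007 |

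This covers admissions only. No corresponding figure was derived for bed days.

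**6. False changes under the null (assumed).** Main simulation:
- 110 Trusts, one third each never-users, always-users and adopters.
- Trust-specific wave with peak at week 15 (SD 1), height 20 to 100 above a floor of 0.5, width SD 3 weeks.
- Adopters start near their own peak, within weeks 11 to 22.
- About 5,000 DDDs and 1,000 admissions a week, with 8% and 5% weekly noise.
- No PCT effect. Random-intercept model with linear week, one PCT indicator (a simplification of the SAP's two) and their interaction. 100 runs.

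| Denominator | Level rejected | Slope rejected | Either |
|---|---|---|---|
| Total admissions | 8% | 2% | 10% |
| COVID-positive admissions | 56% | 98% | 100% |

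Two independent 5% tests would give 1 - 0.95² = 9.75%, so the total-admissions result is about nominal. With the COVID-positive denominator, 11.4% of Trust-weeks were undefined.

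**7. With the quadratic week term of SAP 5.2.4.** Three further null simulations, each under its own assumed values, gave 100% with linear week. With the quadratic term, level or slope was falsely rejected in 37% (60 runs), 48% (60 runs) and 53% (40 runs). The Monte Carlo standard error is √[q(1 - q)/n]: 6.2, 6.4 and 7.9 percentage points. Total admissions gave about 8% to 10%. Some fits in the 48% simulation had convergence warnings.

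**The case against.** The strongest reply is that the plan is a controlled interrupted time series. Never-users and always-users (SAP 4.5.2) contribute the same calendar weeks, and an epidemic-shaped ratio would trigger the non-linear terms of SAP 5.2.4. Both points count. The quadratic roughly halves the false changes or better, so a reader who infers that the plan as written must produce large spurious effects goes too far. But step 6 already includes controls, and step 7 adds the quadratic. The excess remains because the reciprocal of a Trust-specific wave does not cancel under one common curve in week. The occupancy adjustment that SAP 5.2.5 would consider concerns bed days over capacity, not COVID-positive share.

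Three other strong readings are tempting and not supported:
- *The ratio reflects the epidemic and not antibiotic use.* The numerator still enters, so dominated is the right word.
- *Zeros mainly remove pre-introduction weeks.* Small counts can occur at both ends of the window, controls have no introduction date, and the SAP gives no adoption dates. In the main simulation only 1.6% of week-9 Trust-weeks were zero against 11.4% overall.
- *The SAP presents these ratios as antibiotic use in COVID-19 patients.* It does not. Its objective (SAP 1.2) is at Trust level.

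It is also fair to say that every magnitude here rests on assumed counts.

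**Conclusion.** The point holds. The mismatch of populations, the identity in step 3, the undefined value at zero and the missing rule follow from the SAP itself and need no assumption about counts. That false level or trend changes can arise, and survive the controls and the quadratic term, is shown under assumed waves: 37% to 53% of null runs against about 8% to 10% for total admissions. How large the distortion would be here, and how often zeros would occur (61% of Trust-weeks at a mean of 0.5 COVID-positive admissions, 5% at a mean of 3), cannot be stated from the SAP. The defect is confined to these four secondaries and their 5.2.6 versions. The primary outcome and the three secondaries with total denominators are not affected, so this should be changed but does not threaten the main analysis.

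**What to change.** - **5.1.3 and 5.2.6.** Take the COVID-positive-denominator ratios out of hypothesis testing. Keep them, if wanted, as descriptive plots, with a stated rule for zero or very small denominators and a count of the Trust-weeks omitted.
- **5.2.1.** For inference, model tDDDs and CAP-DDDs per total admissions and per total bed days, adding the COVID-positive share p and PCT x p as terms. In 5.2.6, enter the shares positive by day 7 and after day 7 as two covariates instead of two denominators.
- **Interpretation.** If a0 and a1 are DDDs per other and per COVID-positive admission, then D/A = a0(1 - p) + a1·p = a0 + (a1 - a0)p. The share coefficient is therefore the difference between a COVID-positive and another admission, and PCT x p is the change in that difference with PCT. A reader might take the coefficient as DDDs per COVID-positive admission; that would be intercept plus coefficient. All of these are ecological, Trust-level quantities, and the SAP should say so.

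**Cost.** SAP wording only, with the same data. The simple ratio outcomes lose inferential status, and the wording must be aligned with the protocol if it lists them.

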### 5.1.4 ORDER OF TESTING

Not applicable.

### 5.1.5 TIMING, UNITS AND DERIVATION OF SECONDARIES

See 5.1.2.

CAP-DDDs are defined as amoxicillin (IV or oral), ceftriaxone (IV), cefuroxime (IV), clarithromycin (IV or oral), co-amoxiclav (IV or oral), doxycycline (oral), erythromycin (oral) and levofloxacin (IV or oral).

## 5.2 ANALYSIS METHODS

### 5.2.1 LIST OF METHODS AND PRESENTATION

A controlled interrupted time series (ITS) will be undertaken with variable dates of introduction of PCT testing across Trusts (McLintock et al. 2014; Kontopantelis et al. 2015; Bernal et al. 2017, 2018; Bottomley et al. 2019; Bell et al. 2021).

We will fit a linear mixed effects model with ISO week, use of PCT testing (yes/no) in ICU in each ISO week, use of PCT testing (yes/no) in ED/acute wards in each ISO week, and their interaction with ISO week as independent fixed-effect variables, and Trust as a random-effect variable. Based on this ‘segmented’ regression model, we will estimate the level and trend of the rate of antibiotic usage before and after the introduction of PCT testing and test the null hypotheses that 1) the level (i.e. model intercept) and 2) the trend (i.e. model slope) do not change following the introduction of PCT testing.

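### The segmented model has no exposure-pattern terms, so trend differences between kinds of Trust enter coefficients that are tested as the change after PCT introduction

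*SAP*

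**What the plan says.** In SAP 5.2.1 exposure enters through two indicators that may change from week to week: "use of PCT testing (yes/no) in ICU in each ISO week, use of PCT testing (yes/no) in ED/acute wards in each ISO week". Calendar time is a further fixed effect, each indicator also has its own slope over time, and the only random term is for Trust; the SAP words this part as "and their interaction with ISO week as independent fixed-effect variables, and Trust as a random-effect variable". From this model "we will estimate the level and trend of the rate of antibiotic usage before and after the introduction of PCT testing", and the two null hypotheses are that level and trend "do not change following the introduction of PCT testing".

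SAP 4.5.2 defines three exposure groups. Never-users are "Trusts not using PCT (routinely) between ISO weeks 9 and 27". Always-users are "Trusts using PCT in either or both of ICU and ED/acute wards at the beginning of the first wave (ISO week 9") who continue to week 27 without stepping up. Adopters start or increase PCT use in between. The groups are used for summaries that "will be presented by country (England or Wales) and by exposure to PCT testing"; no model in section 5 contains them.

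Section 3.3 keeps all acute and teaching Trusts. Section 5.2.2 gives covariate adjustment as not applicable. Section 5.2.4 allows Trust-specific slopes to be considered, without a trigger. The sensitivity analyses in 5.2.5 (phase-in, occupancy) and the additional model in 5.4 have no exposure-group term.

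**The concern.** An interrupted time series protects against confounding because each unit is compared with its own past. Only adopters have both a past and a future relative to introduction. An always-user has an unchanging PCT status in all 19 weeks, and so does a never-user. In the model as written, the difference between their calendar trends is nevertheless information about the PCT x week coefficients.

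A random Trust intercept absorbs differences in level between Trusts, not differences in slope. If Trusts that already used PCT moved differently through the first wave for other reasons, such as the timing of their local peak or their stewardship practice, that difference is reported as an effect of introducing PCT. It can create an effect where none exists or mask a real one. Both hypotheses for the primary outcome are exposed, as are the secondary outcomes if the same model is used for them.

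**Working it through.** **Inputs from the SAP.** Weeks 9 to 27, so 27 − 9 + 1 = 19 points per Trust (2.3, 2.7); about 100-120 English Trusts (2.3); two-sided 5% tests (3.1); fixed and random effects as in 5.2.1. The SAP states no power or error-rate figure for this model, so there is none to reproduce.

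**Assumed, because the SAP is silent.** 110 Trusts, Trust SD 1, residual SD 0.5, introductions spread over weeks 12-19 in the simulations, and various group sizes and PCT locations. d is a non-causal slope difference per week between always-users and never-users.

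**Step 1: algebra, with one PCT indicator P for clarity.** The mean is a + b·t + g·P + h·P·t plus a Trust intercept.
- Never-user (P = 0 throughout): a + b·t
- Always-user (P = 1 throughout): (a + g) + (b + h)·t

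The slope difference between these groups is h, the coefficient tested as the trend change. With no adopters, the expected estimate of h is exactly d although no Trust introduced anything. With adopters, h is a precision-weighted mix of d and their within-Trust change.

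**Step 2: simulation, one indicator, true PCT effect zero** (60 to 100 runs per row).

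| Never/always/adopter | d | Model | Mean PCT x week | Share of d | Rejected |
|---|---|---|---|---|---|
| 40/30/40 | 0 | as planned | 0.0002 | – | 6% |
| 40/30/40 | −0.02 | as planned | −0.0137 | 0.0137/0.02 = 0.685 | 84% |
| 60/10/40 | −0.02 | as planned | −0.0089 | 0.445 | 42% |
| 60/50/0 | −0.02 | as planned | −0.0205 | 1.025 | 100% |
| 40/30/40 | −0.02 | plus random slope | −0.0105 | 0.525 | 50% |
| 40/30/40, true slope SD 0.02 | −0.02 | plus random slope | −0.0091 | 0.455 | 32% |
| 40/30/40 | −0.02 | plus group and group x week | 0.0002 | about 0 | 3% |

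In the second row the PCT level coefficient, with week coded 0 to 18, averages +0.164 and is rejected in 83%. Its size depends on the week origin: nine weeks later, at week 18, it is 0.164 + 9 × (−0.0137) = 0.041, still not zero.

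A pure level difference of one Trust SD with equal slopes does little harm: level bias 0.02 (rejected in 9%), slope rejected in 6%.

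**Step 3: the planned two indicators.** In the 40/30/40 simulation with d = −0.02, ICU x week averages −0.0105 (0.525d, rejected in 63%) and ED x week −0.0056 (0.28d, rejected in 20%). The generalised least squares expectation, over mixes with 10 to 35 always-users and 35 to 40 adopters, is 0.37d to 0.69d in ICU x week. Other assumed location mixes gave 0.40d to 0.94d for ICU and −0.04d to −0.65d for ED. The split, and even the sign for ED, depends on where always-users tested.

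**Step 4: which repair removes it** (two indicators, same method).
- Always-user, always-user x week and adopter, but no adopter x week: an adopter slope difference d then puts about 0.95d into PCT x week, against 0.26d to 0.59d in the planned model. That is worse.
- The three 4.5.2 groups, each with a week interaction: this removes a difference that is constant within a group. Always-users, however, mix ICU only, ED/acute only and both, and adopters include Trusts stepping up from ICU only. If Trusts with prior ICU use have slope d, 0.35d to 0.44d remains in ICU x week.
- A pattern factor defined by PCT location at week 9, with its week interaction: a linear trend difference that is constant within a pattern lies in the span of the added terms, so it drops out of the PCT coefficients exactly.

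**The case against.** **The objective is wider than introduction.** Section 1.2 asks whether having a pathway with PCT modified the impact of the first wave, and always-versus-never trends bear on that. This is fair as to relevance. But 2.1 and 5.2.1 both define the estimate as change following introduction, and the hypotheses are worded so. The wider contrast can be reported, but under its own name.

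**Trust-specific slopes are available.** Section 5.2.4 permits them, and they help: false rejection falls from 84% to 50%, or to 32% when slopes truly vary. They do not restore 5%, and their use is discretionary.

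**The size is assumption-driven.** This stands. The mechanism follows from the model, but its size needs group sizes, locations and variances that the SAP does not give. It also needs d to differ from zero, for which the SAP offers no evidence either way. What can be said is that the plan relies on parallel trends without stating or checking it.

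**Stronger readings that the SAP does not support.** A reader might infer that the trend estimate is mostly a cross-sectional comparison. That depends on unknown group sizes; in a single-indicator calculation with 60/10/40 Trusts the weight on d is 0.42, under half. A reader might also carry single-indicator results (0.42d to 0.89d over the mixes tried) over to the ICU and ED coefficients. The plan has two indicators, so those figures apply to neither. Nor are baseline level differences a serious problem, since the random intercept absorbs nearly all of them.

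**Conclusion.** The concern holds as an identification problem. The model in 5.2.1 cannot separate adopters' before/after change from trend differences between kinds of Trust, yet its coefficients are tested as the former. The trend is affected directly, and the level as a consequence.

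Under the assumptions above, about 0.4d to 0.7d of an always-user slope difference enters ICU x week, with the ED/acute share depending on where PCT was used. This range illustrates the mechanism; it is not a prediction for this study. The same mechanism applies if the primary model was meant to use the none/partial/full variable that 5.4 mentions. Because both primary hypotheses are affected and the repair needs no new kind of data, the model should be changed before analysis.

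**What to change.** In 5.2.1, add to the primary model, as fixed effects, an exposure-pattern factor and its interaction with ISO week. Refine the 4.5.2 groups by PCT location at ISO week 9:
- never-user
- always-user: ICU only, ED/acute only, or both
- adopter from none
- adopter stepping up from ICU only, or from ED/acute only

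The PCT step and trend changes are then identified by adopters' own before/after change, with non-adopters as concurrent controls for the calendar trend. The adopter x week terms belong in the primary model, not only in a sensitivity analysis, for the reason in Step 4. Report the model without pattern terms, or the always-versus-never contrast, separately and label it a cross-sectional association.

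**Cost.** SAP wording and wider intervals. In the 40/35/35 illustration, three-group terms with week interactions raise the ICU trend SE from about 0.005 to about 0.017. The 95% half-width goes from 1.96 × 0.005 = 0.010 to 1.96 × 0.017 = 0.033 per week. The finer location factor will not be cheaper. Leaving out adopter x week looks less costly (trend SE 0.0044 to about 0.007 with a single indicator), but that model does not isolate the within-Trust change. With 15-20 Welsh hospitals analysed separately, some patterns may be empty or nearly so; the SAP should state in advance how they would be merged.

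### The level change tested in SAP 5.2.1 is the PCT contrast at the model's time origin, not the jump at each Trust's introduction of PCT

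*SAP*

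**What the plan says.** SAP 5.2.1 describes a controlled interrupted time series "with variable dates of introduction of PCT testing across Trusts". The fixed effects are ISO week, a weekly yes/no indicator for PCT in ICU, a second one for ED/acute wards, and "their interaction with ISO week as independent fixed-effect variables, and Trust as a random-effect variable". Two null hypotheses follow: that "the level (i.e. model intercept) and 2) the trend (i.e. model slope) do not change following the introduction of PCT testing".

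SAP 2.7 takes the data "between ISO weeks 9-27 (24 February 2020 to 05 July 2020 inclusive"), and 2.3 gives each Trust a series "with up to 19 weekly data points for each". For Trusts that introduce PCT, 5.1.2 fixes the exposure date: "their first week of PCT use will be defined as the ISO week following the reported introduction date". SAP 4.5.2 also defines always-users, who use PCT from week 9, "continuing to do so until ISO week 27 without increasing the level of usage". They have no introduction inside the window, and nothing in 3.3 or 5.2.1 takes them out of the model.

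The SAP specifies no centring of ISO week, no weeks-since-introduction variable and no contrast at the introduction week.

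**The concern.** In a segmented regression, the level change is the jump at the moment of the intervention. That requires a post-intervention time term that is zero when the intervention starts. Here the post-intervention slope runs on calendar week, so the coefficient that the SAP calls the intercept change sits wherever the week variable is zero. Introduction dates also differ between Trusts, so no single calendar week is the moment of introduction for all of them.

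The first of the two stated hypotheses is therefore not the one that the named coefficient tests. A change in trend alone can be reported as a level change of the opposite sign, and a genuine step is tested with avoidable imprecision. The model in 5.2.1 is the only main model described, so this reaches the primary outcome and the secondary outcomes alike.

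**Working it through.** **Algebra, one PCT indicator.** The model is y = b0 + b1·week + b2·PCT + b3·PCT·week + Trust effect. The PCT effect in week t is b2 + b3·t, so b2 is the effect at t = 0. Let the true effect be a jump L at introduction week t0 plus a slope change S per week afterwards: L + S·(t − t0). Matching terms gives b3 = S and b2 = L − S·t0. The stated null is L = 0, but the coefficient tests L − S·t0 = 0. The two agree only if S = 0, which is the second hypothesis.

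With L = 0, S = −0.05 and a common introduction week:
- t0 = 10: b2 = 0.05 × 10 = +0.50
- t0 = 14: +0.70
- t0 = 18: +0.90
- t0 = 22: +1.10

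Moving the origin to week 9 still leaves 0.05 × (t0 − 9) = +0.05, +0.25, +0.45 and +0.65.

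**Staggered introductions.** The SAP states no effect size, variance or number of Trusts per exposure group, so there is no plan figure to reproduce. All inputs here are assumptions: 40 never-users, 35 adopters, Trust SD 1.0, residual SD 0.5 DDD per admission, 19 weeks, one PCT indicator. First PCT weeks are spread over 11–20, 11–15 or 15–22. Results are generalised least squares expectations under a random intercept, with origin at week 0. Flat means that always-users do not depart from the never-users' level or trend.

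| Assumed truth | Always-users | Level coefficient | Level null rejected | Trend estimate |
|---|---|---|---|---|
| L = 0, S = −0.05 | none | +0.65 to +0.79 | 96–100% | about −0.05 |
| L = 0, S = −0.05 | 30, same trend change | +0.66 to +0.86 | about 100% | about −0.05 |
| L = 0, S = −0.05 | 30, flat | −0.06 to +0.04 | 5–9% | −0.006 to −0.018 |
| L = −0.3, S = 0 | none | −0.30 | 29–73% | 0 |
| L = −0.3, S = 0 | 30, flat | about −0.29 | 83–93% | 0 |

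For a pure step, the jump at introduction is detected with power above 99%. Without always-users, the standard error at week 0 is about 2.0 to 3.6 times that at introduction. For introductions in weeks 11–20 it is 0.137; 0.3/0.137 = 2.19, which gives power of about 59%. With L = −0.3 and S = −0.05 in the same weeks and no always-users, the level coefficient is about +0.41, so a real fall carries the wrong sign.

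**Other origins** (L = 0, S = −0.05).
- Weeks coded 1–19, introductions in weeks 11–20, no always-users: level +0.34, rejected 97% of the time.
- Centred at the middle introduction week, no always-users: −0.001, +0.015 and −0.032 for the three ranges, rejected 5–9% of the time.
- Centred in the same way with 30 flat always-users: about −0.18 to −0.20, rejected about 97% of the time.

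**Check of the remedy.** A separate simulation used 40 never-users and 40 adopters introducing in weeks 12–22, with PCT plus weeks since introduction in the model. True L = 0, S = −0.05 gave a mean level of −0.005, rejected in 4% of runs. True L = −0.3, S = −0.05 gave −0.30, rejected in 100%.

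**The case against.** The best defence is that the hypotheses are worded correctly. They refer to change after introduction, 5.2.5 says that the primary analysis assumes an immediate step, and the bracketed mention of the intercept may be shorthand. An analyst could centre week, or take a contrast at any week from the fitted model. The SAP names no time origin, so week 0 is the literal reading of its silence and not a stated rule. Without always-users, centring at a typical introduction week removes nearly all of the bias and the loss of precision.

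Much of this stands. The trend test does not depend on the origin, and a pure step is estimated with little or no bias. Whether an effect should evolve with calendar week or with time since introduction is partly a modelling choice.

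It does not remove the point. The SAP names the intercept as the tested quantity and gives no origin or contrast, so the sign of the result depends on an unstated coding choice. Centring fails once flat always-users are in the model. Even a derived contrast, b2 + b3·t0, forces the jump to vary linearly with the date of introduction. The phase-in of 5.2.5 is a sensitivity analysis and is not described as moving the time origin.

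**Conclusion.** The point holds as a fault in how the level change is defined. On the model written in 5.2.1, the PCT coefficient is the contrast at the time origin, and both obvious codings put that origin outside weeks 9 to 27. This follows from algebra alone.

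The size does not. Under the assumptions above, a trend change without a jump leads to rejection of the level null anywhere from about the nominal rate (5–9%) to 96–100%, depending on how many always-users there are and how they behave. Where the level test looks sound because flat always-users dilute it, the trend estimate is cut from −0.05 to between −0.006 and −0.018.

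A reader might infer that the planned analysis will almost certainly report a false level change, or that no centring could ever help. The SAP supports neither: it does not give the mix of Trusts, always-users belong to the planned data, and one centring value works well when they are absent. Nor does the argument about the origin invalidate the trend test; that test is affected only through the way always-users enter it.

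**What to change.** In 5.2.1, for each setting (ICU, ED/acute wards):
- Replace the PCT × ISO week interaction by PCT_it × (week − first PCT week_i), set to zero before introduction, and keep calendar week and the PCT indicator.
- Give Trusts already using PCT in that setting at week 9 their own intercept and slope terms, so that they do not enter the introduction effect. This part is essential, because those Trusts have no first PCT week inside the window.
- Define the level change as the PCT coefficient at the first PCT week and the trend change as the weeks-since-introduction coefficient. State both null hypotheses in those terms.

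The cost is SAP wording and a few derived variables. The introduction dates are already collected under 5.1.2, and 4.4.3 already excludes Trusts whose date cannot be obtained.
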